| Respiratory, thoracic and mediastinal disorders                                                                                                                                                                                                                                                                                                                                                                                                                         |                                                                                                                                                                                                                                                                                                                                                                                                                                        |                                                                    |
| Dyspnea ≥ grade 2
Hypoxia ≥ grade 2
Pneumonitis/pulmonary infiltrates ≥ grade 2
Pulmonary fibrosis ≥ grade 2
Cough ≥ grade 3                                                                                                                                                                                                                                                                                                                                | Hold all therapy until interstitial lung disease is ruled out. 

• If non-infectious interstitial lung disease is confirmed, oxaliplatin must be discontinued.

• If non-infectious interstitial disease is ruled out and infection (if any) has resolved, patients with persistent Grade 2 dyspnea or hypoxia can resume treatment at the discretion of the investigator.

 |                                                                    |
| a Hold until improved to less than moderate symptom intensity on the next treatment day.
b Hold oxaliplatin for persistent moderate intensity grade 2 neuropathy. When improved to less than moderate intensity , resume treatment with dose modification for oxaliplatin. If moderate intensity Grade 2 toxicity persists after 4 weeks of delay, discontinue oxaliplatin. Continue 5-FU + LV and irinotecan while oxaliplatin is held. |                                                                                                                                                                                                                                                                                                                                                                                                                                        |                                                                    |

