| Grade 2                                                                    | Maintain dose                                                                | Maintain dose                                                                                                                                              |
| Grade 3                                                                    | ↓ one dose level                                                             | ↓ one dose level                                                                                                                                           |
| Grade 4                                                                    | ↓ one dose level                                                             | Discontinue                                                                                                                                                |
| Other clinically significant AEs: d               |                                                                              |                                                                                                                                                            |
| Grade 2                                                                    | Maintain dose                                                                | Maintain dose                                                                                                                                              |
| Grade 3                                                                    | ↓ one dose level                                                             | ↓ one dose level                                                                                                                                           |
| Grade 4                                                                    | ↓ one dose level                                                             | Discontinue                                                                                                                                                |

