| Grade 3                                                                            | First episode:
Decrease oxaliplatin one dose level
a
Second episode:
Discontinue oxaliplatin | Discontinue oxaliplatin                                         |
| Respiratory, thoracic and mediastinal disorders                                    |                                                                                                                                                           |                                                                               |
| Laryngopharyngeal
dysesthesia                                                   | 1-7 day duration
(intermittent or continuous)                                                                                                          | > 7 day duration
(intermittent or continuous)                              |
| Grade 1
Grade 2                                                                 | Maintain dose and consider increasing infusion time of oxaliplatin to 6 hours                                                                             | Maintain dose and consider increasing infusion time of oxaliplatin to 6 hours |
| Grade 3                                                                            | At the investigator discretion, either discontinue oxaliplatin or increase duration of infusion to 6 hours                                                | Discontinue oxaliplatin                                                       |
| Grade 4                                                                            | Discontinue oxaliplatin                                                                                                                                   | Discontinue oxaliplatin                                                       |
| Respiratory, thoracic and mediastinal disorders                                    |                                                                                                                                                           |                                                                               |

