| a Hold oxaliplatin for persistent moderate intensity grade 2 neuropathy. When improved to less than moderate intensity , resume treatment with dose modification for oxaliplatin. If moderate intensity Grade 2 toxicity persists after 4 weeks of delay, discontinue oxaliplatin. Continue 5-FU + LV while oxaliplatin is held. |                                                                                                                                                                                                                                                                                                                                                                                                                                           |

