**8.2.3 Treatment management for patients receiving mFOLFIRINOX**

mFOLFIRINOX dose modifications for patients treated with mFOLFIRINOX are detailed in Table 8.2.3.2. Dose modifications are based on the dose level changes outlined in Table 8.2.3.1.

Additionally, the following dose modification instructions must be followed:

All doses must be based on the AE requiring the greatest modification.

Any chemotherapy doses that have been reduced may not be escalated.

- If  $\geq$  grade 2 toxicity occurs **during the 46-48 hour infusion of 5-FU**, discontinue the infusion and refer to Table 8.2.3.2 for dose modifications for the next cycle of mFOLFIRINOX.
- The leucovorin dose remains 400 mg/m^2 regardless of changes in the 5-FU, oxaliplatin, and irinotecan doses. If 5-FU is held, leucovorin should also be held.
- If oxaliplatin is discontinued, treatment should continue with 5-FU, leucovorin, and irinotecan.
- If irinotecan is discontinued, treatment should continue with 5-FU, leucovorin, and oxaliplatin.
- If 5-FU and leucovorin are discontinued, treatment should continue with irinotecan and oxaliplatin.

Table 8.2.3.1: Dose levels for mFOLFIRINOX

|                                                                                                                                                                              | Dose Level 0
Starting Dose
(mg/m  ) | Dose Level -1
(mg/m  ) | Dose Level -2
(mg/m  ) | Dose Level -3 |
|------------------------------------------------------------------------------------------------------------------------------------------------------------------------------|---------------------------------------------------------------------|----------------------------------------------|----------------------------------------------|----------------------|
| Oxaliplatin                                                                                                                                                           | 85                                                                  | 65                                           | 50                                           | Discontinue          |

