| Leucovorin*                                                                                                                                                           | 400                                                                 | 400                                          | 400                                          | Discontinue          |
| 5-FU infusion                                                                                                                                                         | 2400                                                                | 1920                                         | 1600                                         | Discontinue          |
| Irinotecan                                                                                                                                                            | 150                                                                 | 135                                          | 120                                          | Discontinue          |
| *Levoleucovorin at 200 mg/m  can be substituted for leucovorin per institutional practice or as needed for drug availability (see Appendix II ). |                                                                     |                                              |                                              |                      |

Table 8.2.3.2. Treatment management for mFOLFIRINOX -(See Table 8.2.1.3 for oxaliplatin-specific toxicities.)

| Important table instructions:                                                                                                                                                                                                                                                                                                                                                                                                                                                                                                                                                                                              |                                                                                                                                        |                                                                                                                           |

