| Grade 3                                                                                                                                                                                                                                                                                                                                                                                                                                                                 | Increase duration of infusion to 6 hours                                                                                                                                                                                                                                                                                                                                                                                               | Discontinue oxaliplatin                                            |
| Grade 4                                                                                                                                                                                                                                                                                                                                                                                                                                                                 | Discontinue oxaliplatin                                                                                                                                                                                                                                                                                                                                                                                                                | Discontinue oxaliplatin                                            |

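### Table 8.2.1.3 has no grade 4 neuropathy row, and the only written control-arm fallback, read literally, can keep oxaliplatin going where grade 3 would stop it

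*Combined protocol and SAP*

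**What the plan says.** **Control arm.** The heading of Table 8.2.1.2 (mFOLFOX6) refers oxaliplatin-specific toxicities to Table 8.2.1.3. Section 8.2.2 sends CAPOX patients to both tables for the same purpose. In Table 8.2.1.3 the neuropathy block has rows for grades 1, 2 and 3 and is followed directly by the respiratory block. Grade 3 lasting 1-7 days lowers oxaliplatin one level at the first episode and stops it at the next ("Second episode"). Grade 3 lasting longer than 7 days stops it outright. The respiratory block of the same table does have a grade 4 row: grade 4 laryngopharyngeal dysesthesia stops oxaliplatin.

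The last row group of Table 8.2.1.2 is "Other clinically significant AEs". For grade 4 it gives one level down if the event has resolved before the next cycle, and discontinuation if the event delays that cycle. Footnote b defines resolved as grade 1 or less on the next Day 1. Footnote d leaves it to the investigator whether an event is clinically significant.

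**Triplet arm.** Section 8.2.3 states that "mFOLFIRINOX dose modifications for patients treated with mFOLFIRINOX are detailed in Table 8.2.3.2". That table prints its own neuropathy and respiratory rows, including a grade 4 neuropathy row that says to discontinue without naming a drug. Its heading nevertheless reads "Treatment management for mFOLFIRINOX -(See Table 8.2.1.3 for oxaliplatin-specific toxicities".

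**The concern.** A dose-modification table should never give a milder action for a more severe grade of the same toxicity. With no grade 4 row, a control-arm site that looks up grade 4 neuropathy is left with the catch-all row. That row sorts events only by whether they delay the next cycle. It has no rule for duration and none for repeat episodes, and those are the two conditions under which grade 3 stops oxaliplatin.

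What is at stake is individual patient safety. Section 10.2 describes both acute and cumulative oxaliplatin neurotoxicity as dose-limiting and ties the likelihood of neurotoxicity to the total dose given. In some cases the written rule would continue the drug after the worst non-fatal grade.

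**Working it through.** No sample size, power or alpha figure is involved. The check sets the two rules side by side and asks whether oxaliplatin is stopped.

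**Inputs.**
- Grade 3 actions: Table 8.2.1.3.
- Grade 4 actions: the catch-all row of Table 8.2.1.2 with footnotes b and d. The table instructions apply level changes to 5-FU and oxaliplatin.
- Oxaliplatin levels: 85, 65, 50 mg/m², then discontinue (Table 8.2.1.1, mFOLFOX6); 130, 100, 85 mg/m², then discontinue (Table 8.2.2.1, CAPOX).
- Cycle length: 14 days for mFOLFOX6, 21 days for CAPOX (Tables 7.2.1 and 7.2.2).

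| Control-arm neuropathy | Grade 3 | Grade 4 via catch-all row | Grade 4 milder? |
|---|---|---|---|
| 1-7 days, first episode, resolved | oxaliplatin one level down | one level down | no |
| Over 7 days, resolved by next Day 1 (case A) | stop oxaliplatin | one level down | yes |
| 1-7 days, second episode, resolved (case B) | stop oxaliplatin | one further level down | yes |
| Event delays the next cycle | by duration and episode | discontinue | no |

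**Window for case A.** The event must last more than 7 days but settle within the cycle. That is at most about 8-13 days on mFOLFOX6 and 8-20 days on CAPOX, and less if it starts later in the cycle.

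**Dose kept in the next cycle.**
- Case A, from full dose: 65/85 = 76% (mFOLFOX6); 100/130 = 77% (CAPOX).
- Case B, after one earlier reduction: 50/85 = 59%; 85/130 = 65%.
- Grade 3 rule in either case: 0%.

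A patient already at level -2 reaches discontinuation under either rule, so there is no inversion there.

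**Do the general rules close the gap?**
- The highest-grade rule in Section 8.2 concerns several toxicities occurring together.
- The greatest-modification rule in Section 8.2.1 and Table 8.2.1.2 chooses among adverse events. It does not send a single grade 4 event back to the grade 3 row.
- For CAPOX, Table 8.2.2.2 governs capecitabine. Section 8.2.2 lets oxaliplatin continue when capecitabine is held or stopped, unless it is contraindicated.

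**With the row added.** If Table 8.2.1.3 stopped oxaliplatin at grade 4 in both duration columns, the number of inverted cases would fall from two to none.

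**The triplet heading.** The two tables differ in wording:
- For grade 3 laryngopharyngeal dysesthesia of 1-7 days, Table 8.2.1.3 says "At the investigator discretion, either discontinue oxaliplatin or increase duration of infusion to 6 hours" and the triplet table says "Increase duration of infusion to 6 hours". A 6-hour infusion satisfies both.
- For grades 1-2 of that event, the control table says to consider the longer infusion and the triplet table says to use it.
- Table 8.2.1.3 footnote a ends "Continue 5-FU + LV while oxaliplatin is held". Triplet footnote b repeats the persistent grade 2 rule and adds irinotecan to the drugs continued.
- Triplet footnote a asks for a hold until "less than moderate symptom intensity" without naming the drug.
- At grade 4 neuropathy, Table 8.2.1.3 has no row that could conflict with the triplet's own.

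**The case against.** The strongest reply is that no text orders grade 4 neuropathy into the catch-all row. Neuropathy is a listed oxaliplatin toxicity, so it is not obviously an *other* event, and entry is discretionary. On that view the control-arm text is simply silent on grade 4. This stands in part. A reader might infer that the protocol instructs sites to continue oxaliplatin after grade 4 neuropathy, and the documents do not support that. Section 8.2 calls the modifications recommended and asks only that deviations be documented, and Section 12.2 ends treatment for unacceptable adverse events. An investigator could also apply the grade 3 rule as the lesser case. But the catch-all row is the only written grade 4 route in the control arm, and nothing requires the stricter action.

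Second, the cases are narrow. Section 10.2 describes acute neurotoxicity as usually reversing within hours or days, and cumulative neurotoxicity as easing over months. The latter would normally delay the cycle, where the catch-all row already discontinues. This stands, and it is why the point is minor.

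Third, a reader might turn the rule into a large excess dose: a grade 4 event in cycle 1 of mFOLFOX6 leaves 7 × 65 = 455 mg/m² still permitted. That is a ceiling for one extreme patient. The lowest cumulative dose with a quoted risk in Section 10.2 is 780 mg/m² (10%), above the full planned courses of 8 × 85 = 680 and 5 × 130 = 650 mg/m². The documents give no frequency by grade, duration or episode, so no patient count follows.

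Fourth, a reader might infer that the pointer in the triplet heading puts triplet patients under conflicting orders on stopping oxaliplatin. It does not: Section 8.2.3 names Table 8.2.3.2, which prints its own rows, and none of the differences above is a contradiction on stopping the drug.

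**Conclusion.** Wrong as written; minor; patient safety. Table 8.2.1.3 lacks a grade 4 neuropathy row. Taken literally, the only written control-arm fallback gives a milder oxaliplatin action at grade 4 than at grade 3 in two cases: an event of over 7 days, or a second episode of 1-7 days, in each case down to grade 1 or less by the next Day 1. In those cases 59% to 77% of the starting dose continues where the grade 3 rule gives none.

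This assumes that the published table is complete, that the investigator uses the catch-all row, and that the patient is not already at level -2. The first is likely: the grade 3 row runs directly into the next block, and the parallel triplet block keeps its grade 4 row. Such cases should be uncommon and their number cannot be derived.

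The point does not extend to the trial's results. A reader might infer that differing neuropathy rules compromise the comparison of arms, but no endpoint, power, alpha or analysis figure depends on this table, and the DFS test is by intention to treat. Nor do the documents show that the unqualified discontinuation in the triplet grade 4 row was meant for oxaliplatin alone. Section 8.2 permits that reading without requiring it.

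**What to change.** Add a grade 4 neuropathy row to Table 8.2.1.3 that discontinues oxaliplatin in both duration columns, as the table already does for grade 4 laryngopharyngeal dysesthesia. Section 8.2.1 already says that 5-FU and leucovorin continue once oxaliplatin is discontinued.

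As tidying only, delete the pointer to Table 8.2.1.3 from the Table 8.2.3.2 heading, so that the triplet's own rows plainly govern.

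Leave the triplet grade 4 neuropathy row unchanged unless the sponsor confirms that only oxaliplatin was meant. Narrowing it on a guess could loosen a safety rule.

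The cost is a protocol table edit and a memo to sites. Sample size and analysis do not change.
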